### Timeline

Baseline data collection is being conducted in March 2023, after verification but before randomisation and notification of participants on their allocation. Delivery of the intervention will be over 10 months beginning April 2023. Endline will be conducted 24 months post baseline (March 2024). The process evaluation and qualitative research will be conducted shortly after completion of the delivery of InBusiness, in January-March 2024. A description of activities and timelines is in Table 2.

**Table 2 Tab2:** Schedule of enrolment, interventions and assessments

	**Study period**							
	**Enrolment**	**Allocation**	**Post-allocation (10 months)**					**Endline**
**Timepoint**	***-t***_***1***_	**0**	***2***	***4***	***6***	***8***	***10***	***24 months***
**Enrollment**								
** Eligibility screen**	X							
** Informed consent**	X							
** Allocation**		X						
**Interventions**								
*** Classroom training***			X	X	X	X	X	
*** Capacity building***			X	X	X	X	X	
*** Business growth kits***			X	X	X	X	X	
*** PPI trainings***			X	X	X	X	X	
*** Procurement***			X	X	X	X	X	
**Assessments**								
*** Baseline survey***	X	X						
*** Endline survey***								X
*** Process evaluation***							X	

### Data analysis

A detailed analysis plan will be published before the endline survey. The analysis will estimate intention-to-treat (ITT) effects.

We will assess the quality of the balance achieved by randomisation by describing the arms of the trial at baseline in terms of the primary and secondary outcomes and sociodemographic variables. If there is evidence of imbalance, based on subjective interpretation of the magnitude of the difference, then we will plan a priori to include such variables in the main analysis of the primary and secondary outcomes.

We will estimate the effect of the intervention by comparing the proportions (e.g. unmet need for disability-related goods and services) and the means/medians (e.g. household expenditures, economic empowerment score) between the arms of the trial. We will report the unadjusted estimated effects as risk ratios for binary outcomes and difference in the means for continuous outcomes. In the final analysis, to increase the precision of the estimates and reduce the risk of bias from imbalances at baseline, we will use regression to adjust for the baseline levels of the outcome, stratification variables and variables considered to be imbalanced at baseline. For binary outcomes, we will model the risk ratio with a modified Poisson regression [20]. For continuous outcomes, we will use linear regression. Where sufficient power allows, we will also disaggregate by ME characteristics such as gender and disability type.

Transcripts of in-depth interviews from RCT participants and programme implementers will be coded using NVivo 12 and analysed thematically [21]. Coding frameworks will be developed using the semi-structured interview guides as a starting point and additional codes included iteratively. Comparisons and interrelationships between themes and sub-groups (e.g. by gender, impairment type) will be conducted throughout the analysis. The process evaluation will also use data from the endline RCT and monitoring data from LftW on the receipt and user experience of different components of InBusiness. This data will be tabulated, and regressions used to explore differences amongst InBusiness participants (e.g. by gender, location, impairment type).

### Ethics and dissemination

Ethical approval has been received from the Institutional Review Boards at the London School of Hygiene and Tropical Medicine (UK) and the AMREF Health Africa Ethics and Scientific Review Committee (Kenya).

Written informed consent will be sought from all participants by experienced data collectors who underwent a 1-week training on study protocols, immediately prior to administering the survey or beginning an interview. All participants will be over 18 years of age, though some may have mild/moderate intellectual impairments that affect their ability to give true informed consent. Capacity to consent amongst all participants will be assessed through an “Evaluation to Sign Consent” [22], which asks participants five questions about their understanding of the information sheet. Participants who are unable to provide a satisfactory response even with clarifications will be deemed unable to provide true informed consent. In these instances, parents/guardians will provide their consent, and the participant will provide assent if they are still able to participate in data collection. Adaptations will be in place to support the direct participation of people with different impairments (e.g. sign language interpretation, simplified interview schedules and information sheets).

Data from participants will be anonymised, with the exception that programme implementers may be identified by job title unless requested otherwise during the informed consent process. Data storage and management protocols are governed by a Data Protection Impact Assessment and data management plan. Data will not be made publicly available as it would not be possible to provide a minimum dataset that would allow for reproduction of findings without possible identification of participants.

No specific discomfort, distress or hazards are expected as a result of any component of the research (participating in survey and/or in-depth interviews). Participants may feel uncomfortable discussing their experiences but will be reminded that they have the right to stop or refuse to answer any questions at any time, for any reason. Participants (with the exception of programme implementers) will receive a one-off payment of KSH 500 to compensate for their time and other costs linked to participating in the research.

LftW has in place separate monitoring procedures to report and address any harms arising from participation in the InBusiness programme. LSHTM takes primary responsibility for the design of the study and ensuring it meets appropriate standards. KEMRI will lead the data collection and ensure that it meets ethical requirements. KEMRI and LSHTM will be in regular conduct regarding the running of the trial, including on data collection, data analysis and dissemination of findings. Any concerns or instances of misconduct related to participating in the research (i.e. survey, in-depth interview) can be reported to the LSHTM Research Governance and Integrity Office ([contact]) or the Scientific Ethics Review Unit at KEMRI ([contact]), which is separate from the research team. Annual reports on study progress will be reviewed by the LSHTM Ethics Committee. LftW is responsible for the delivery of InBusiness and for monitoring and addressing any harms that result from participation in the InBusiness programme. The trial team and LftW will meet quarterly to discuss the delivery of the InBusiness programme and the trial conduct.

The study funder (United Kingdom Foreign, Commonwealth and Development Office) will not be involved in data collection or management, analysis or publication decisions. LftW and other programme implementers were consulted during the study design, to ensure that trial outcomes were in line with the intended outcomes of the InBusiness programme. They will also be consulted to discuss preliminary findings, but ultimate decisions on if and what to publish will be made by the research team. Authorship on any papers or reports will be determined according to standard guidance [23]. Any significant protocol modifications will be updated within the trial registry [23].

Findings from the research will be disseminated to academic and nonacademic audiences through journal articles, short reports/infographics with main findings and in-person and online events. The initial findings will be shared back and verified with participants through in-person events in the counties where the trial took place.

## Discussion and impact

There are some limitations of this evaluation. First, only single masking (of individuals conducting analyses for RCT) is possible in an intervention of this nature. To minimise bias, we have stressed in the informed consent process that responses will not impact the receipt of any services and have chosen several outcome measures that are less subjective (e.g. household consumption). Second, some impacts of InBusiness may not be apparent in the 2-year follow-up period and require a longer time period to develop. We have mitigated this risk by choosing indicators that the research team and the programme implementers felt are likely to show positive change if the programme’s theory of change is correct. Finally, it is possible that some impacts, particularly sub-group analyses by gender and other characteristics, may be underpowered.

Still, InBusiness is an important programme to evaluate for several reasons. The InBusiness programme is a large-scale intervention that is being delivered across eight counties across Kenya, with potential for scale-up in the future. Data on the effectiveness of InBusiness can therefore build a case for continued investment in the programme — including potential adaptations and expansion to other context — and/or indicate areas through which to improve the programme. Further, this study on the impact of the InBusiness programme will be one of the few trials of a livelihoods intervention that targets people with disabilities and caregivers of people with disabilities [12]. Findings from this research therefore have the potential to inform the design and delivery of not only the InBusiness programme but also other disability-inclusive livelihood programmes. Governments, NGOs and other actors have limited resources to invest in programmes such as InBusiness, particularly given cuts to foreign aid and rising cost of living crises. The lack of evidence on the effectiveness of livelihood interventions amongst people with disabilities hinders informed policymaking and planning, a gap which can begin to be filled through evaluations of promising programmes such as InBusiness.

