### Data collection

Data for the RCT will be collected using questionnaires completed by participants in the intervention and control arms at baseline and endline. Data collection will be conducted in a place of the participants’ choosing (e.g. home, business). The questionnaire is based upon standard modules and from modules used in other studies (Table 1). It includes sections on the following: household composition, housing conditions, food security, savings and expenditures; individual economic empowerment, well-being and access to services; and microenterprise revenues, costs and practices. It was reviewed by programme implementers and piloted with individuals who had previously participated in the InBusiness programme to check for acceptability and understanding before full-scale data collection. The survey will take approximately 1 h to complete and will be delivered by trained enumerators using Open Data Kit (ODK).

**Table 1 Tab1:** Outcome indicators for the RCT of the InBusiness programme

Outcome indicator	Description	Source
*Primary outcomes*		
Household consumption	Overall per capita household consumption and domains of expenditures (food, health) adjusted for inflation	Adapted version of [14]
Economic empowerment	Score on a 14-item financial self-efficacy tool	Adapted version of [15]
*Secondary outcomes*		
Subjective wellbeing	Total score on a 7-item tool on self-reported well-being	Adapted version of [16]
Food security	Proportion classified as facing moderate or severe food insecurity	Food Insecurity Experience Scale [17]
Social attitudes	Total score on 9-item tool on social attitudes	World Health Model Disability Survey [18]
Unmet need for disability-related goods and services	Self-reported unmet need for disability-related healthcare, assistive devices or assistance	Tool developed for study
Microenterprise profits	Net of revenues minus costs, adjusted for inflation	Tool developed for study

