### Outcomes

A theory of change was created in collaboration with programme implementers to identify anticipated outcomes of the InBusiness programme. The ultimate aim of InBusiness is to improve the livelihoods of microentrepeneurs of people with disabilities and their households, which can lead to reduced poverty and improved well-being. The primary outcome measure is changes in household expenditures and economic empowerment (Table 1). Secondary outcome measures will include subjective well-being, food security, social attitudes, unmet need for disability-related goods and services and microenterprise profits. Indicators are tied to the existing tools where possible.

The endline survey will also collect information from the intervention arm about their experience participating in the programme, including the following: (a) details on receipt of different components of the intervention to explore fidelity and uptake (e.g. what was received, frequency, how delivered), (b) satisfaction with the programme overall and with specific components, (c) challenges experienced during any component of the intervention, and (d) self-reported impacts of participation.

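### The protocol overstates that only analysts can be masked: nothing in it requires endline enumerators to know the arm while they ask the outcome questions

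*Protocol article*

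**What the plan says.** Under Discussion and impact, the protocol article names masking as the first limitation: "only single masking (of individuals conducting analyses for RCT) is possible in an intervention of this nature". It offers two mitigations. Participants are told at consent that their answers do not affect the services they receive, and the authors "have chosen several outcome measures that are less subjective (e.g. household consumption").

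Other sections describe how outcomes are collected:

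- **Data collection:** the survey takes about an hour and "will be delivered by trained enumerators using Open Data Kit (ODK"), at a place the participant chooses, such as home or business.
- **Table 1:** the primary outcomes are household consumption ("Overall per capita household consumption and domains of expenditures (food, health) adjusted for inflation") and economic empowerment ("Score on a 14-item financial self-efficacy tool").
- **Ethics and dissemination:** "KEMRI will lead the data collection and ensure that it meets ethical requirements", whereas "LftW is responsible for the delivery of InBusiness".
- **Design:** baseline is collected before randomisation.
- **Outcomes:** "The endline survey will also collect information from the intervention arm about their experience participating in the programme". This is the only part of the survey described as specific to one arm. Its position in the form is not given.

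**The concern.** The limitation treats two questions as one. Participants know whether they were offered the programme, and those who deliver it know whom they serve; neither group can be masked. Whether the person asking the endline questions must know the arm is a separate matter, and the article gives no reason why they must.

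An enumerator who knows the arm may probe expenditure items or clarify self-efficacy items differently between arms. Nothing later in the plan would remove such a difference. Intention-to-treat analysis governs who is compared, not how outcomes were recorded. Baseline interviews precede allocation, so adjusting for baseline levels cannot correct a difference that arises only at endline. Masked analysts would receive data that already carry it.

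Of the two mitigations, the consent wording addresses participants' motives, not interviewers' conduct. Describing consumption as less subjective helps only in part: consumption is still recalled by the participant and recorded by an enumerator, and the other primary outcome is a self-efficacy score.

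**Working it through.** **Step 1. Does any section require enumerators to know the arm?**

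| Question | What the article says | Section |
|---|---|---|
| Who allocates? | University staff, using R | Recruitment and randomisation |
| Who delivers the programme? | The lead NGO | Ethics and dissemination |
| Who collects the data? | A separate research institute | Ethics and dissemination |
| When is baseline? | Before randomisation, so the arm does not yet exist | Design; Timeline |
| What endline content depends on the arm? | The programme-experience questions | Outcomes |
| Where does that content sit in the form? | Not stated | – |

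No section requires allocation to reach enumerators before or during the outcome questions. The impossibility claim is therefore unsupported for endline enumerators.

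**Step 2. How else could the arm become known?**

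- A tailored in-kind asset (Intervention) may be visible at a home or business visit (Data collection).
- Answers on business practices, costs or services may hint at training, assets or procurement links.
- Participants may simply say so.

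None of these is certain to reveal the arm. Controls may use other programmes (Usual care), so an asset alone does not prove allocation. But masking could only be partial.

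**Step 3. Illustration of scale.** The plan has no figure on masking to reproduce. Inputs from Sample size are mean 7811 KSH, SD 3124 KSH, 199 analysed per arm and a target effect of 10%.

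- Target effect: 0.10 × 7811 = 781.1 KSH; 781.1 / 3124 = 0.25 SD.
- Standard error of the difference: 3124 × √(2/199) = 313.2 KSH.
- With no true effect and a between-arm recording shift b, the chance of a significant two-sided 5% result is 1 − Φ(1.96 − b/SE) + Φ(−1.96 − b/SE).

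| Assumed shift, % of mean | KSH | b/SE | False-positive risk |
|---|---|---|---|
| 0 | 0 | 0 | 5.0% |
| 1 | 78.1 | 0.249 | 5.7% |
| 2 | 156.2 | 0.499 | 7.9% |
| 3 | 234.3 | 0.748 | 11.6% |
| 5 | 390.6 | 1.247 | 23.9% |

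For the empowerment score, in SD units with SE = √(2/199) = 0.100, assumed shifts of 0.05, 0.10 and 0.20 SD give 7.9%, 16.9% and 51.4%.

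Every shift here is an assumption; the article gives none.

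**Step 4. Effect on the stated sample size.** Masking enumerators changes no input, so 398 analysed and 497 recruited are unaffected. For the record, n per arm = 2(z_α + z_β)² × SD² / δ² gives 198 at one-sided 5% and 252 at two-sided 5%, so the plan's 199 matches only a one-sided test. That is a separate matter; 199 is used here simply as the planned analysed number per arm.

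**The case against.** The best defence is that the limitation is disclosed, and that the phrase about the nature of the intervention has a plausible basis. With interviews at homes and businesses, visible assets, questions on business practices and participants who know their arm, the authors may have judged that assessor masking could not be promised. Consent is taken by data collectors immediately before the survey, which gives an early chance of disclosure. Some participants may have intellectual impairments or need interpreters, so asking them not to mention the programme may fail. Both primary outcomes are self-reported by people who know their arm, and enumerator masking leaves that source of bias in place. Module order and enumerator scripts belong in the questionnaire or manual, which a condensed article need not show.

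Much of this stands, and it limits the point. A reader might infer that masking would come free from reordering the electronic form. The article does not support that: allocation must also be withheld, and other routes to unmasking remain. Nor can one infer that the programme module is the only thing that reveals the arm, or that it is wrongly placed, since the form order is not shown. Nor does any section show that interviewer bias would favour the intervention; that is a reasonable worry, not a documented fact.

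What does not stand is the defence of the sentence itself. The article makes a positive claim that nothing beyond analyst masking is possible. Masking that is difficult or partial is not impossible, and leaving detail to another document does not excuse a statement that is too broad.

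**Conclusion.** The point holds as a correction to a stated design choice. The nature of the intervention excludes masking participants and deliverers. It does not exclude keeping endline enumerators unaware of allocation while they ask the outcome questions, and both primary outcomes depend on those enumerators.

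Its size cannot be derived from the article. The illustrative rise from 5% to about 8% to 24% rests on assumed recording shifts of 2% to 5% of mean expenditure, 199 analysed per arm, the assumed SD, a two-sided 5% test and no true effect. It shows only that small shifts matter when the target effect is 0.25 SD; it is not evidence that such shifts would occur. The benefit is confined to the interviewer's share of any bias.

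**What to change.** Revise the limitation under Discussion and impact to say that participants and deliverers cannot be masked, but that endline enumerators will be kept unaware of allocation as far as possible until the outcome modules are complete. To support this:

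1. Do not show allocation to enumerators.
2. Place the intervention-only experience module after all primary and secondary outcome modules, or confirm that it is already there.
3. Ask participants not to mention the programme until that module opens.
4. Have enumerators record whether, when and how they learned the arm.

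The cost is form design and a training note before endline, with no added staff and no change to the sample size. The downside is that masking will be partial, because participants may disclose and assets may be seen. The revised text should say so, and should state that participants' own reporting bias remains.

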### Trial status

This is protocol version 2, which has been accepted by Ethics Committees at the London School of Hygiene & Tropical Medicine, Kenya Medical Research Institute and AMREF Health Africa Ethics and Scientific Review Committee (Kenya). Participant recruitment began on March 6, 2023, and ended March 24, 2023. This protocol paper was originally submitted during participant recruitment, but the resubmission with clarifications was treated as a new submission.

## Data Availability

The dataset is not possible to anonymise in a way that would allow for reproduction of findings without identifying participants.
